### Interventions

2.3

#### The experimental group

2.3.1

The experimental group receiving JPQC combined with mesalazine. JPQC decoction pieces, sourced from the hospital's herbal medicine room, will be administered twice a day, 0.5 h after breakfast and dinner. Mesalazine enteric-coated tablets, 1.0 g per dose, will be given three times a day, 1 h after each meal. The interval between taking JPQC and Mesalazine tablets is 0.5 h.

#### The control group

2.3.2

The control group receiving mesalazine alone.

### Outcomes

2.4

#### Primary outcome

2.4.1

The primary outcome of the study is the inflammatory bowel disease fatigue scale(IBD-F), which will be measured at baseline and 4, 8, 12 weeks after randomization. The IBD-F consists of 3 parts. Possible scores are 0–20 and 0–120 in part I and II, respectively. If the ‘not applicable – N/A’ (not applicable) option is checked (questions 3, 4, 9, 12, 13, 14), a corrected result has to be calculated from the following formula: Corrected result = actual total result/(120 – number of N/As × 4) × 120 [19].

#### Secondary outcomes

2.4.2

The secondary outcomes include the following items.

##### Inflammatory Bowel Disease Questionnaire (IBDQ)

2.4.2.1

IBDQ covers four dimensions: intestinal symptoms, systemic symptoms, emotional ability, and social ability, with a total of 32 questions, with 1–7 options for each question, with 1 for the worst and 7 for the best options. The IBDQ is a total score of 4 dimensions, with higher scores representing higher quality of life [20].

##### TCM symptom efficacy

2.4.2.2

TCM symptom efficacy evaluation criteria will refer to the TCM Symptom Score Table for Gastrointestinal Diseases [21]. The scores of 0, 3, 5, and 7 represented no symptoms, mild, moderate, and severe symptoms, respectively, where the main symptoms included abdominal pain, diarrhea,mucous purulent bloody stool, tenesmus, anal burning, and the secondary symptoms included dry mouth with bitter taste in mouth, poor food intake and poor appetite, fatigue, lazy word.

##### The disease activity

2.4.2.3

The modified Mayo score [15] and simple clinical colitis activity index (SCCAI) [22] will be recorded to assess the disease activity.

### Mechanism outcomes

2.5

The procedure involves the detection and analysis of intestinal microbial diversity and non-targeted metabonomics. To conduct this, it is essential to collect freshly excreted feces, preferably from the first bowel movement in the morning. Approximately 2 g of the middle section of the feces should be carefully extracted and deposited into a sterile fecal collection tube. Two distinct fecal samples need to be collected sequentially, with detailed information such as name, sex, age, and sampling time noted for each specimen. These outcomes are measured before and after treatment.

### Safety outcomes

2.6

The main safety indicators include laboratory tests before and after treatment, encompassing blood routine, urine routine, fecal routine, occult blood, liver and kidney function, and electrocardiogram.

### Statistical analysis

2.7

Statistical analysis will be conducted using SPSS 24.0 software. Descriptive statistics for measurement data will include mean ± standard deviation ($\bar{X}$ ± S) for data conforming to normal distribution. Two independent samples t-tests will be employed for comparing means, and variance analysis for multi-sample comparisons. Nonparametric tests will be used for data not conforming to normal distribution. Counting data will be analyzed using the χ^2^ test, and rank sum test for rank data. Correlation analysis between two variables will use linear correlation for bivariate normal distribution data and Spearman rank correlation for non-bivariate normal distribution or graded data. A significance level of *P* < 0.05 will be considered statistically significant. The study will also provide statistical descriptions of adverse events, adverse reactions, dropout rates, and rejections during treatment.

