#### Sample sizes

2.2.6

Based on the literature findigns, the control group treated with mesalazine showed a 12-week effective rate of 71 % [17], while the experimental group treated with JPQC recipe and mesalazine exhibited an effective rate of 94.12 % in 12 weeks [18]. Considering a clinical difference to improve the effective rate, with α set at a unilateral level of 0.05 and β at 0.10, the sample size calculation was performed using the formula$$n=\frac{{2\bar{p}\bar{q}\left(Z_{\alpha }+Z_{\beta }\right)}^{2}}{{\left(p1-p2\right)}^{2}}$$

This yielded a sample size of approximately 56 cases for each group (n1 = n2 ≈ 56 cases). Accounting for a dropout rate of 20 %, the study required a total of 140 cases, with 70 patients in the control group and 70 patients in the test group.

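### No IBD-F part or visit is named as the primary endpoint, so up to six primary tests at P < 0.05 are permitted; the stated t-test also makes no use of baseline as a covariate

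*Protocol article*

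**What the plan says.** Section 2.4.1 (Primary outcome) names the IBD-F, "which will be measured at baseline and 4, 8, 12 weeks after randomization". On scoring it says "Possible scores are 0–20 and 0–120 in part I and II, respectively", and it adds a rescaling to 120 when items are marked not applicable. It does not say which part is primary, which visit is primary, whether the value analysed is the follow-up score or the change from baseline, or what result counts as success. Table 1 schedules the IBD-F at week 24 as well, but section 2.4.1 does not list that visit.

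Section 2.7 (Statistical analysis) is one general paragraph for all outcomes: "Two independent samples t-tests will be employed for comparing means, and variance analysis for multi-sample comparisons". It continues: "Nonparametric tests will be used for data not conforming to normal distribution". The threshold is a P value "< 0.05 will be considered statistically significant", without a stated sidedness. No multiplicity rule, baseline covariate or centre term appears, and the paragraph does not refer to another document for the primary analysis.

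Section 2.2.6 (Sample sizes) is based on week-12 response rates of 71% and 94.12%, "with α set at a unilateral level of 0.05 and β at 0.10".

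**The concern.** A primary endpoint needs a variable, a time point and one comparison. Here the variable has two versions (0–20 and 0–120), the time point has three candidates, and the test may be parametric or rank-based depending on how the data look. Each route is judged at the same 0.05. If the choice is made after the results are known, or if any significant result is taken as success, the real false-positive rate of the primary claim is well above 5% and cannot be stated.

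The second issue is distinct and smaller. Every patient contributes a baseline IBD-F, yet the only two-group method stated for a mean has no covariate. That does not bias the comparison or raise its type I error, but it gives up precision. This matters because the trial was sized on a response rate, so the documents establish no power for a comparison of IBD-F means.

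**Working it through.** **1. The plan's own figure.** Inputs from section 2.2.6: p1 = 0.71, p2 = 0.9412, power 90%, and the printed formula n = 2·p̄·q̄·(Zα + Zβ)² / (p1 − p2)².

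- p̄ = (0.71 + 0.9412)/2 = 0.8256, so 2·p̄·q̄ = 0.2880; (p1 − p2)² = 0.2312² = 0.05345.
- Two-sided 0.05: (1.960 + 1.282)² = 10.507, so n = 0.2880 × 10.507 / 0.05345 = 56.6. This matches the stated 56 or so.
- One-sided 0.05, as stated: (1.645 + 1.282)² = 8.564, so n = 46.1. This does not match.
- Dropout: 56 / (1 − 0.20) = 70 per arm, 140 in total. This matches.

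I use 56 evaluable patients per arm and two-sided 0.05 below, because that is the level at which the stated size reproduces. The mismatch in sidedness is a separate matter.

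**2. False positives if the open choices are all used.** Two parts × three visits = 6 tests. Under independence the chance of at least one false positive is 1 − 0.95^k:

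| Tests | Which | Independent |
|---|---|---|
| 2 | both parts, one visit | 9.8% |
| 3 | one part, three visits | 14.3% |
| 6 | both parts, three visits | 26.5% |

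The scores will be correlated, and the documents give no correlations, so these are assumed. Two-sample t-tests were simulated with 56 per arm and 20,000 replicates, with equal correlation between visits and a second correlation between parts:

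| Between visits / between parts | One part, 3 visits | Both parts, 3 visits |
|---|---|---|
| 0.3 / 0.3 | 13.3% | 24.5% |
| 0.5 / 0.5 | 12.6% | 22.1% |
| 0.7 / 0.7 | 10.8% | 17.8% |
| 0.8 / 0.8 | 9.8% | 14.9% |

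These count errors in either direction. Counting only false claims in favour of JPQC, six two-sided tests give about 11% at 0.5/0.5 and 7% at 0.8/0.8, against a nominal 2.5%. If each test were one-sided at 0.05, the figures would be about 20% and 14%, against a nominal 5%.

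**3. Precision.** Let ρ be the correlation between baseline and follow-up IBD-F, with equal SD at both times. Relative to a t-test on follow-up values (variance 1), ANCOVA has variance 1 − ρ² and a change-score t-test has 2(1 − ρ).

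| Assumed ρ | ANCOVA | Cut | Change score | ANCOVA n per arm for the same power as 56 |
|---|---|---|---|---|
| 0.3 | 0.91 | 9% | 1.40 | 51 |
| 0.5 | 0.75 | 25% | 1.00 | 42 |
| 0.7 | 0.51 | 49% | 0.60 | 29 |

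The last column is 56 × (1 − ρ²). Since 1 − ρ² = (1 − ρ)(1 + ρ) and 1 + ρ ≤ 2, ANCOVA is never less precise than the change score. Below ρ = 0.5 the change score is worse than ignoring baseline.

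**The case against.** The strongest reply is that section 2.7 is a generic paragraph in a condensed article. It ties no test to the IBD-F, a part or a visit, and a list of measurement times is not a list of hypothesis tests. Both sizing rates are week-12 rates, so week 12 may be the intended endpoint. In that case only the part is open, and two correlated tests at 0.05 give about 8–9% for correlations of 0.8–0.5. Model detail such as covariates may sit in an analysis plan that is not shown.

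Much of this stands, and it limits what can be claimed. A reader might infer three stronger things that the documents do not support:

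- **That the plan is six t-tests, any of which counts as success.** This is not written. The text permits it and does not prevent it, so six is an upper count for the visits in section 2.4.1.
- **That baseline is ignored and that this inflates false positives.** A t-test on change from baseline is not excluded. In a randomised comparison on one endpoint, leaving baseline out costs precision only.
- **That the analysis of variance would treat repeated scores as independent.** The wording does not say what samples are compared, and it rules out neither a repeated-measures form nor a comparison across the three centres.

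What does not stand is that the gap can be left to another document. The score and time point of the primary outcome belong in the section that defines it, and that section leaves both open. Even if the part were settled, three undesignated visits would give about 10–14%.

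**Conclusion.** The point holds in this form. The primary outcome has no designated part or visit, and the stated analysis sets one 0.05 threshold with no multiplicity rule and a data-dependent choice of test. If both parts are tested at all three visits, the two-sided familywise error is 26.5% under independence and about 15–25% over the assumed correlations; with one part it is about 10–14%. The exact value depends on correlations that the documents do not give and on how the choice is eventually made. The direction does not: every reading that leaves the part or the visit open exceeds 5%.

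The loss of precision is a separate and secondary point. Its size (9%, 25% or 49% of variance against follow-up values alone) rests entirely on assumed baseline correlations, since no IBD-F SD or correlation is reported. The undesignated endpoint must be settled before any comparative look at the data; the baseline adjustment is a strong recommendation.

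**What to change.** In section 2.4.1, name one IBD-F score at week 12 as the single primary endpoint. Week 12 is the end of treatment and the time point of the sizing rates. Part I is one reasonable choice, because the not-applicable rescaling to 120 concerns the other score; Part II is equally valid if the investigators consider it closer to the trial's aim. List the other part and the other visits as secondary.

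In section 2.7, for this endpoint, replace the t-test with ANCOVA on the week-12 score, adjusting for baseline IBD-F and centre. A repeated-measures mixed model over weeks 4, 8 and 12 with the week-12 contrast as the primary result would also serve. Report the difference with its 95% CI and state the sidedness. Keep the rank test as a sensitivity analysis, so that the primary method does not depend on the look of the data.

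The cost is a few sentences in two sections and slightly more analysis work, with no extra patients or visits. The real concession is giving up the other chances to declare primary success. Keeping all six tests with a Bonferroni correction is possible, but each would then need P < 0.05/6 = 0.0083.

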**Methods:**

In this randomized clinical trial, 140 subjects diagnosed with UC will be recruited and randomized into two groups. They will receive either JPQC combined with mesalazine or mesalazine alone for 12 weeks. Follow-up visits will be conducted every four weeks, with a post-treatment visit scheduled at 6 months. The primary outcome measures include the Inflammatory bowel disease fatigue scale(IBD-F). Secondary efficacy indicators comprise the assessment of TCM syndrome and individual syndrome efficacy before and after treatment, Modified Mayo score, Simple clinical colitis activity index (SCCAI), as well as the Inflammatory Bowel Disease Questionnaire (IBDQ) for each group. The other outcomes are the Intestinal microbial diversity and non-targeted metabonomics, which will be measured at baseline and 12 weeks after randomization.

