**Fig. 1 fig1:**
[figure not shown]
The flow chart of the trial.

This is a randomized controlled multicenter clinical trial comprising two parallel groups. From January 2024 to June 2025, 140 patients meeting the diagnostic criteria and syndrome types of UC will be recruited. During the recruitment process, potential participants meeting the inclusion criteria will be thoroughly informed about the study's purpose, examinations, intervention measures, and follow-up procedures. Upon obtaining informed consent, eligible subjects will be randomly assigned to two groups in a 1:1 ratio. The groups will receive either JPQC combined with mesalazine or mesalazine intervention for 12 weeks. The UC patients will be followed up again after 6 months. The schedule details are listed in Table 1.

**Table 1 tbl1:** Schedule of trial.

Period	enrollment	baseline	treatment			follow-up
time points	week-1	week 0	week 4	week 8	week 12	week 24
patients						
Informed consent	✓					
Inclusion/Exclusion criteria	✓					
Medical history	✓					
Physical examination	✓					✓
Laboratory examination	✓					✓
Randomization	✓					
Intervention						
Jianpi Qingchang decoction(JPQC) group	JPQC:two times daily; + mesalazine: 1g/three times daily					
Mesalazine control group	1g/three times daily					
Outcomes						
Inflammatory bowel disease fatigue scale(IBD-F)		✓	✓	✓	✓	✓
Inflammatory Bowel Disease Questionnaire (IBDQ)		✓	✓	✓	✓	✓
TCM symptom efficacy		✓	✓	✓	✓	✓
Modified Mayo score		✓			✓	✓
Simple clinical colitis activity index (SCCAI)		✓				
Intestinal microbial diversity and non-targeted metabonomics		✓			✓	
Trial evaluation						
Safety of medicine		✓	✓	✓	✓	✓
Adverse event		✓	✓	✓	✓	✓
Reasons of drop-outs or withdrawals		✓	✓	✓	✓	
Patient's compliance					✓	

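### Section 2.7 names no paired or repeated-measures method, although its main outcomes are measured repeatedly in the same patients

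*Protocol article*

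**What the plan says.** Section 2.7 (Statistical analysis) fixes the tests by name. For means: "Two independent samples t-tests will be employed for comparing means, and variance analysis for multi-sample comparisons". For non-normal data: "Nonparametric tests will be used for data not conforming to normal distribution". Counts get the chi-square "test, and rank sum test for rank data". Linear or Spearman correlation is added for associations. No paired test, repeated-measures analysis of variance or mixed model is named, and no test is tied to a particular comparison.

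On design, section 2.1 states: "This is a randomized controlled multicenter clinical trial comprising two parallel groups", with patients "randomly assigned to two groups in a 1:1 ratio".

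On the data:
- Table 1 schedules IBD-F, IBDQ and TCM symptom efficacy at weeks 0, 4, 8, 12 and 24. Section 2.4.1 lists the primary outcome, IBD-F, at baseline and weeks 4, 8 and 12, without singling out one of them.
- The abstract lists among the secondary indicators "TCM syndrome and individual syndrome efficacy before and after treatment".
- Section 2.5, on stool microbiota and metabolites: "These outcomes are measured before and after treatment".
- Section 2.6 gives as safety indicators "laboratory tests before and after treatment".

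**The concern.** The repeated values come from the same patients and are therefore correlated. The only t-test that 2.7 names assumes two unrelated samples, as do the rank sum and chi-square tests. With two arms, a multi-sample comparison of means most naturally refers to visits, and the variance analysis assigned to it is not said to allow for repeated measures.

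Two different misapplications are possible, and they err in opposite directions. Testing before against after as if they were two groups of patients makes the standard error too large, so a real shift in a laboratory value or stool measure can be missed. Entering several visits per patient as separate observations in a between-arm test makes the standard error too small, so an arm effect is declared too easily. Because the primary outcome is listed at several visits with none singled out, a multi-visit analysis of it is a realistic prospect.

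**Working it through.** The plan states no figure for this point, so there is none to reproduce. The check asks what happens if the named tests are put to the repeated data.

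**Inputs**
- Patients per arm: 56, from section 2.2.6 (70 per arm less 20% dropout: 70 × 0.80 = 56).
- Post-baseline visits for the primary outcome: 3 (weeks 4, 8, 12; section 2.4.1).
- Nominal two-sided level 5% (P < 0.05 in section 2.7; two-sided is assumed here).
- Within-patient correlation ρ: not in the document. Assumed 0.3, 0.5 and 0.7, equal between all pairs of visits, with the same SD at each visit.
- True before/after shift for the power figures: assumed 0.3 SD.

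**1. Before/after data tested as two independent samples**

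In SD units, the independent t-test uses SE = √(2/n). The true SE of the mean change is √(2(1−ρ)/n). The ratio is 1/√(1−ρ).

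The actual type I error is approximately 2[1 − Φ(1.96/√(1−ρ))]. At ρ = 0.5: 1.96 × 1.414 = 2.77, which gives 0.0056.

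For power with a 0.3 SD shift, 0.3/√(2/56) = 1.587.
- Independent test: 1 − Φ((1.96 − 1.587)/√(1−ρ)). At ρ = 0.5: 0.373/0.707 = 0.527, which gives 30%.
- Paired test: 1 − Φ(1.96 − 1.587/√(1−ρ)). At ρ = 0.5: 1.96 − 2.245 = −0.285, which gives 61%. Simulation with t-tests gives 60%.

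| ρ | SE ratio | Type I error, independent test (simulated) | Power, independent (simulated) | Power, paired (simulated) |
|---|---|---|---|---|
| 0.3 | 1.20 | 2.0% | 33% | 46% |
| 0.5 | 1.41 | 0.6% to 0.7% | 30% | 60% |
| 0.7 | 1.83 | 0.05% | 24% to 25% | 81% |

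The paired test keeps about 5% type I error throughout.

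**2. Three post-baseline visits pooled as independent rows in a between-arm test**

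The variance of the arm mean is understated by the design effect 1 + (3−1)ρ. The actual type I error is approximately 2[1 − Φ(1.96/√(1+2ρ))].
- ρ = 0.3: √1.6 = 1.265; 1.96/1.265 = 1.549; 12.1% (simulated 12.1%).
- ρ = 0.5: √2.0 = 1.414; 1.96/1.414 = 1.386; 16.6% (simulated 16.6%).
- ρ = 0.7: √2.4 = 1.549; 1.96/1.549 = 1.265; 20.6% (simulated 21.3%).

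**3. The named t-test used between arms, one value per patient**

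Simulated type I error at ρ = 0.3, 0.5 and 0.7:
- week 12 values: 5.1%, 4.7%, 4.8%;
- change from baseline: 5.0%, 4.8%, 4.8%.

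The level is held, because each patient contributes one value and the arms are independent.

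**The case against.** The strongest reply is that the document does not say it will run the analyses checked in steps 1 and 2. Repeated-measures analysis of variance is a variance analysis, and the sentence on nonparametric tests can cover the signed-rank or Friedman test. With three recruiting hospitals (section 2.2.1), a multi-sample comparison could also mean centres, whose patients are independent. Sections 2.5 and 2.6 say when measurements are taken, not that a within-arm test will follow. Changes can be compared between arms with the t-test that is named. Finally, this is a condensed article, and a full protocol or analysis plan may hold the model details.

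Most of this stands, and it rules out a stronger reading. A reader might infer that 2.7 contains only independent-sample tests and that the trial's P values will therefore be wrong. The text does not support that: two of the named methods are open, no within-arm test is explicitly planned, and the between-arm comparison can be done validly with the test named. The type I inflation depends on pooling visits as separate rows, which the document does not state.

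The reply does not remove the point. Section 2.7 does more than leave detail out. It commits to tests by name, and the t-test it names does not fit the before/after framing used in three other places. Its method for multi-sample comparisons is left open exactly where the choice between independent and repeated measures decides whether the result is valid.

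**Conclusion.** The point holds conditionally. Section 2.7 names no paired or repeated-measures method for outcomes that are repeated in the same patients, and it does not say which test serves which comparison.

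The consequence depends on use. Applied to before/after data, the independent t-test is too conservative and loses about half the power in the central case. Applied to pooled post-baseline visits, an independent-samples analysis has two to four times the nominal type I error. Used between arms at one visit or on change scores, the named test is sound. The efficacy comparison is therefore at risk only if visits are pooled.

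All sizes rest on assumed correlations of 0.3 to 0.7, equal between visits, and the power figures also on an assumed 0.3 SD shift. The direction of each error holds for any positive correlation. The wording should be changed before analysis.

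**What to change.** In section 2.7:

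1. Replace the variance analysis for multi-sample comparisons with a repeated-measures mixed model for outcomes measured at several visits (IBD-F, IBDQ, TCM scores). Use patient as subject, with terms for arm, visit, arm-by-visit and baseline value, and report the between-arm contrast as the result.
2. For any before/after contrast within an arm, name the paired test: paired t for means, Wilcoxon signed-rank for non-normal or ordinal data, McNemar for binary data. Label these results descriptive.
3. State that secondary, stool and laboratory outcomes are judged on the between-arm difference.

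If repeated-measures analysis of variance was what the authors meant, saying so would resolve the ambiguity, but the mixed model remains the better statement because it fixes the between-arm contrast and the baseline term.

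The cost is a few sentences in 2.7 and slightly more analysis work. No new data, visits or patients are needed.

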## Abstract

**Background:**

Ulcerative colitis (UC) is a chronic non-specific inflammatory intestinal disease, categoried under "dysentery" and "intestinal bleeding" in Traditional Chinese Medicine (TCM). Jianpi Qingchang decoction (JPQC) is a combination formula specifically designed for the treatment of UC. The primary objective of this study is to examine the clinical efficacy of JPQC in individuals diagnosed with UC who exhibit both spleen deficiency and dampness-heat syndrome, along with the presence of fatigue. The investigation will focus on assessing the impact of JPQC on the gut microbiota and metabolites in these patients, aiming to elucidate the regulatory mechanism that JPQC exerts on the gut microbiota and metabolites in the context of UC-related fatigue.

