TCM exhibits unique advantages in combating fatigue by regulating gut microbes, protecting nerve centers, enhancing antioxidant enzyme activity, reducing metabolite accumulation, and influencing energy metabolism [35]. The JPQC prescription, designed to invigorate the spleen and replenish qi, primarily employs Qi-tonifying herbs to restore spleen Qi. Notably, Qi-tonifying herbs have demonstrated the ability to regulate intestinal flora, restoring diversity and balance [36]. Clinical studies have demonstrated that the combination of JPQC with mesalazine exerts a distinctive synergistic mechanism on the intestinal flora and metabolites of patients with ulcerative colitis (UC) by downregulating erysipelatoclostridium and decreasing the levels of 4-pyrimidine methanamine (hydrochloride), hydroxyprolyl-isoleucine, and L-glutamate. Notably, these three metabolites play a role in anti-inflammatory processes and contribute to enhanced amino acid metabolism [37]. The investigation into whether JPQC further influences UC with fatigue by regulating the disorder of intestinal flora and its metabolites presents an intriguing and crucial research topic.

The primary aim of our study is to explore the impact of JPQC on the intestinal flora and metabolites of patients with UC with spleen deficiency damp-heat type and fatigue. The study aims to investigate the clinical effects of JPQC on patients with UC with spleen deficiency and dampness-heat syndrome accompanied by fatigue, along with its regulatory mechanism on intestinal flora and metabolites. This research will contribute valuable insights into TCM's role in managing UC-related fatigue and may pave the way for novel therapeutic approaches.

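### The single P < 0.05 rule in section 2.7 makes no exception for the microbiome and untargeted metabolome outcomes; feature-level results should be declared under false discovery rate control and labelled exploratory

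*Protocol article*

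**What the plan says.** Section 2.7 (Statistical analysis) is the article's only analysis section. It lists tests by data type. For group comparisons of continuous data it says "Two independent samples t-tests will be employed for comparing means, and variance analysis for multi-sample comparisons", with nonparametric, chi-square and rank sum tests for other data. For associations it says "Correlation analysis between two variables will use linear correlation for bivariate normal distribution data", and Spearman correlation otherwise. One threshold follows: a P value below "0.05 will be considered statistically significant". No class of outcome is set apart, and no multiplicity adjustment is mentioned.

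Section 2.5 (Mechanism outcomes) says "The procedure involves the detection and analysis of intestinal microbial diversity and non-targeted metabonomics" and then describes stool sampling. It gives no feature-level analysis and no number of taxa or metabolites. The abstract (Methods) places these among the other outcomes, "which will be measured at baseline and 12 weeks after randomization".

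The article describes the rank of these outcomes in two ways. The abstract (Background) says "The primary objective of this study is to examine the clinical efficacy of JPQC", and section 2.4.1 makes IBD-F the primary outcome. The Discussion says "The primary aim of our study is to explore the impact of JPQC on the intestinal flora and metabolites of patients with UC".

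**The concern.** Untargeted profiling measures many features at once. A threshold of 0.05 per test limits the error rate of each test, but not the share of wrong findings in the list that results. If the rule is followed literally for individual taxa and metabolites, some will be declared changed by JPQC even if JPQC changes none of them.

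Feature-level claims appear to be intended. The abstract promises to elucidate how JPQC regulates the gut microbiota and metabolites. The Discussion presents earlier clinical work on JPQC with mesalazine by naming one taxon and three metabolites that decreased. What is at stake is the reliability of the mechanistic conclusion. The clinical comparison on IBD-F is not touched.

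**Working it through.** **Inputs from the article.** The threshold is 0.05 (section 2.7). Section 2.2.6 plans 70 patients per group with 20% dropout, so 70 × 0.80 = 56 per group remain. The article gives no feature count and no error rate for these outcomes, so it has no figure of its own to reproduce.

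**Assumptions.** The number of features m, the share π that truly changes, and the standardised effect d per changed feature are all assumed and shown over a range. Tests are taken as two-sided, because section 2.7 does not state sidedness.

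**Step 1: nothing changes.** Expected false positives = 0.05 × m:
- m = 100: 5
- m = 500: 25
- m = 2,000: 100

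This does not depend on features being independent. The chance of at least one false positive does: for 100 independent features it is 1 − 0.95^100 = 99.4%.

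**Step 2: power per feature at 56 per group.** Power ≈ Φ(d × √(56/2) − 1.96).
- d = 0.3: Φ(1.587 − 1.96) = 0.355
- d = 0.5: Φ(2.646 − 1.96) = 0.754

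**Step 3: false share among declared features.** False share = (1 − π) × 0.05 / [(1 − π) × 0.05 + π × power]. For example, with π = 5% and power 0.50: 0.0475 / (0.0475 + 0.025) = 66%.

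| Truly changed | d = 0.3 (power 0.355) | power 0.50 | d = 0.5 (power 0.754) |
|---|---|---|---|
| 20% | 36% | 29% | 21% |
| 10% | 56% | 47% | 37% |
| 5% | 73% | 66% | 56% |
| 1% | 93% | 91% | 87% |

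**Step 4: when false findings are the majority.** Setting the false share to one half gives π = 0.05 / (0.05 + power). False findings outnumber true ones only if the share truly changed is below:
- 20% at power 0.20
- 9.1% at power 0.50
- 5.9% at power 0.80
- 4.8% at power 1.00

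**Step 5: the alternative rule.** Benjamini-Hochberg at q = 0.05 was simulated with independent features, d = 0.5, 56 per group and 2,000 repetitions per setting. The mean false share was 4% to 5% when 5% to 20% of features truly changed. In the same settings the unadjusted rule gave about 55% (5% changed), 37% (10% changed) and 21% (20% changed).

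With m = 1,000 and 50 features truly changed, the unadjusted rule declared about 85 features, about 47 of them false, so about 85 − 47 = 38 true. Benjamini-Hochberg declared about 11, with a mean false share of about 5%.

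**The case against.** The strongest objection is that section 2.7 never mentions taxa, metabolites or features, and section 2.5 describes only sampling. A journal article condenses the protocol, and the handling of feature-level multiplicity is commonly left to an analysis plan. This stands in part. The absence of a false discovery rate from the article is not in itself an error, and an adjustment may already be planned elsewhere. What remains is that the article does state a rule, in general terms and without exception. If another document says otherwise, the published rule still needs a qualifying clause.

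A reader might infer several stronger points that the article does not support:

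- **That the plan prescribes unadjusted P values.** The sentence gives a threshold and does not say whether P is raw or adjusted. Only the literal reading, with no adjustment mentioned, leads to the figures above.
- **That most declared features will be false.** This needs a small true share. With 20% of features changed and d = 0.5, about one declared feature in five is false. Nothing in the article fixes the share or the effect.
- **That a taxon-by-metabolite correlation screen is planned.** Section 2.7 names no variables for its correlations, so no count of chance correlations can be derived.
- **That microbial diversity must mean a large family of tests.** It could mean a few summary indices. The argument is firmest for the untargeted metabolomics.

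It is also fair to say that a hierarchy partly exists. IBD-F is the only primary outcome, the abstract lists the stool outcomes among the others, and the Discussion's verb is to explore. Against this, the same Discussion sentence calls these outcomes the primary aim, and nowhere does the article label their results as exploratory.

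**Conclusion.** The point holds as a cheap improvement. Read literally, the one rule in section 2.7 would let false feature-level findings grow in proportion to the number of features tested: 5, 25 or 100 expected when nothing changes, for an assumed 100, 500 or 2,000 features. For true shares from 20% down to 1%, and effects of 0.3 to 0.5 SD at 56 per group, the false share runs from 21% to 93%. It would be lower if more features change or if effects are larger.

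Two things limit confidence. That the rule governs feature-level tests is inferred from its general wording, and every input apart from the threshold and the group size is assumed. The conflict between the Discussion's primary aim and the abstract's primary objective is on the page and needs no assumption.

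**What to change.** In section 2.7, limit the P < 0.05 rule to IBD-F and the clinical outcomes. Add that feature-level microbiome and metabolome results, and any feature-level correlations that are run, will be declared by the Benjamini-Hochberg false discovery rate within each family (for example q < 0.05) and reported as exploratory. If an analysis plan already provides this, one sentence pointing to it is enough.

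In the Discussion, reword the primary aim so that it agrees with the abstract's primary objective and with IBD-F as the primary outcome in section 2.4.1, leaving flora and metabolites as the mechanistic aim.

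The cost is a few sentences and a standard adjustment step, with no change to patients, visits or sample size. The real downside is fewer declared features, including some true ones: in the 1,000-feature example, about 11 in place of about 85.
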